## Background

Globally, stroke is the second leading cause of mortality and disability among adults over 60 years old [1, 2]. Due to an aging population, dietary changes, pronounced work-related stress, and rapid economic development, there is an increasing prevalence of stroke among younger individuals [3]. Constipation is a common complication after stroke [4]. Population-based studies indicate that approximately 30% to 60% of stroke patients suffer, or have suffered, from constipation following stroke [5–8]. This wide range can likely be attributed to the adoption of different time points [5, 7, 8], the diagnostic criteria used to measure constipation [4, 5] and patient characteristics [5, 6]. Constipation can severely impair a patient’s quality of life and rehabilitation [9]. Consequently, constipation incurs a heavy burden on patients, patients’ families, and society as a whole [10].

Treatments for constipation after stroke vary and include lifestyle changes [11–13], diet changes [14–18], use of laxatives, enemas, prokinetic drugs, and surgically implanted neuro-modulation [19]. Unfortunately, many of these treatments are poorly tolerated or rejected, or there may be a lack of clinical evidence supporting their use. Thus, there is a need for a safe, effective, and non-toxic therapy for constipation after a stroke.

Acupuncture has a history of more than 2000 years in China and plays an important role in traditional Chinese medicine [20]. A recent systematic review indicated that acupuncture is safe and tolerable, and may improve weekly spontaneous bowel movements (SBMs), quality of life, and constipation symptoms [21]. Acupuncture may, therefore, be an effective treatment for post-stroke constipation and it has several advantages compared with other therapies [22]. However, using acupuncture to treat constipation has not been validated with high-quality clinical evidence. In addition, clinical research focusing on acupuncture for constipation after stroke is rare [19]. Therefore, we designed this trial to assess the preliminary effects and inform future sample size calculations for studies of acupuncture for constipation following an ischemic stroke. Our hypothesis is that the effectiveness of acupuncture is no less than that of mosapride and better than routine health care.

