### Randomization and allocation concealment

Participants will be randomly assigned to one of three groups (the acupuncture group, the medication group, or the control group) using a 1:1:1 ratio. The generation and allocation of a random sequence for group assignment will be conducted by the Research Centre of Clinical Epidemiology, which is affiliated to Peking University Third Hospital in China. Individuals involved in participant randomization will be blinded and will not participate in the recruitment and inclusion of participants. The block randomization method (block size of 6) will be adopted to generate the random sequence, using the Statistical Analysis System (V.9.1.3; SAS Institute Inc., Cary, North Carolina, USA). Opaque computer-generated sealed envelopes will be produced for the randomization and allocation. The envelopes will be numbered consecutively with a serial number on the outside and will contain the allocation information. An envelope will be opened when a participant enters the study after the baseline measurements have been taken. Participants will be allocated to one of the three groups and receive an intervention according to their group allocation. The random allocation sequence and the opaque sealed envelopes will be kept separately by two specific researchers.

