#### Recruitment and baseline assessment

Researchers will recruit participants from outpatient clinics and inpatient wards of the acupuncture and moxibustion departments. Recruitment posters will be posted in the hospital. The posters will contain a brief, Institutional Review Board-approved introduction to the study, the participants, the interventions, and contact information for the researchers. The recruitment information will also be uploaded to the hospital website (http://www.bjzhongyi.com).

Consent will be obtained by one of the investigators, with a witness present. Following written informed consent, eligible patients will be asked to complete a general information form including name, gender, age, medical history, etc. and complete a 1-week defecation diary as the baseline assessment. A neurologist will determine the Glasgow Coma Scale score and the National Institute of Health Stroke Scale score for each participant and these scores will be used to decide whether to include the patient in the study according to the inclusion and exclusion criteria. Personal information about potential and enrolled participants will be collected and maintained confidentially.

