#### Inclusion criteria

Inclusion criteria are a diagnosis of ischemic stroke according to the diagnostic criteria specified by the World Health Organization [23], constipation symptoms according to the Rome IV Functional Constipation Criteria [24], 2 weeks to 6 months after stroke onset, aged between 30 and 75 years old, Glasgow Coma Scale score ≥ 7 and National Institute of Health Stroke Scale ≤ 21, no previous medical history of constipation before stroke onset and symptoms of constipation present for at least 2 consecutive weeks after stroke, no use of gastrointestinal drugs 1 week before randomization (except for emergency drugs), no acupuncture treatment for constipation in the previous 2 weeks, and signed informed consent form.

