### Outcome measures

#### Primary outcome measure

The primary outcome measure will be the change in the weekly mean number of CSBMs over the 4 weeks of the intervention and the 4 weeks of the follow-up. A CSBM is defined as a SBM unrelated to the administration of laxatives or finger manipulation, accompanied by a self-reported feeling of complete evacuation. Bowel movements achieved with the help of glycerin, enemas, or finger manipulation are not considered spontaneous. If bowel movements occur within 24 h after the intake of laxatives, they will not be considered spontaneous. However, if bowel movements occur more than 24 h after administration of laxatives, they will be considered spontaneous. The total number of CSBMs during the treatment period and follow-up period will be averaged to obtain mean weekly CSBMs.

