### Statistical analysis

The analysis of the primary outcome will be based on both a full analysis (intention-to-treat analysis) and per-protocol sets (per-protocol analysis). The analyses of secondary outcomes will be based on the per-protocol sets. The full analysis set refer to the participants who are randomized and receive at least one treatment session. Any missing data will be replaced by the last measured value. The per-protocol sets will be defined as the participants who receive all treatment sessions and completed the study according to the protocol.

The statistical analysis will be performed by a statistician who is blinded to participant group allocation and will not be involved in other aspects of the study. The SPSS statistical package (version 18.0, International Business Machines Corporation, China) will be used to analyze the data. All data will be kept in duplicate by specific researchers. The results of the quantitative data analyses will be presented as means ± standard deviation. The Kolmogorov–Smirnov test will be applied as the normality test for quantitative variables. The Wilcoxon test or analysis of variance (ANOVA) will be used to compare the difference between groups according to the results of the Kolmogorov–Smirnov test. The results for categorical data will be compared with the chi-squared test and presented as a percentage. The statistical significance level will be set at 0.05 (two-sided) with a 95% confidence interval.

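### The article fixes an unadjusted ANOVA or Wilcoxon comparison although baseline CSBMs, stroke severity and time since stroke are available for every participant and plausibly prognostic: valid, but it gives up precision.

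*Protocol article*

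**What the plan says.** All places are in the protocol article.

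- **Outcome.** Under Primary outcome measure: "The primary outcome measure will be the change in the weekly mean number of CSBMs". Baseline CSBMs therefore enter the comparison by subtraction only.
- **Test.** Under Statistical analysis: "The Wilcoxon test or analysis of variance (ANOVA) will be used to compare the difference between groups", with a Kolmogorov–Smirnov test deciding between the two. No covariate is named. The section adds: "The statistical significance level will be set at 0.05 (two-sided) with a 95% confidence interval".
- **Allocation.** Under Randomization and allocation concealment: "The block randomization method (block size of 6) will be adopted to generate the random sequence", with three arms allocated "using a 1:1:1 ratio". No stratification factor is described.
- **Who enters.** Under Inclusion criteria, patients qualify "2 weeks to 6 months after stroke onset", with an NIHSS of up to 21 and a Glasgow Coma Scale score from 7 upwards. Under Recruitment and baseline assessment: "Researchers will recruit participants from outpatient clinics and inpatient wards".
- **What is known at baseline.** The same recruitment section has every participant keep a 1-week diary and be scored on both stroke scales by a neurologist. The only stated use of the scores is the eligibility decision.

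**The concern.** The entry criteria admit a wide mix: early and late after stroke, mild to fairly severe, ward and clinic. As described, neither the allocation nor the analysis takes account of that mix, apart from subtracting baseline CSBMs. Blocking keeps arm sizes level but does nothing for patient characteristics.

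Two things follow. Variation between patients that baseline data could explain stays in the error term and widens every interval. And with 40 per arm, a chance imbalance in a prognostic factor goes uncorrected in the observed contrast.

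This bears on the trial's purpose. The Discussion says the pilot is to inform later sample sizes through effect sizes and variability. An adjusted difference and a residual SD serve that better than their unadjusted counterparts. The Wilcoxon branch neither adjusts nor directly yields the mean difference that a later calculation would need.

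**Working it through.** **The plan's own figure.** 3 × 40 = 120, which agrees with the stated total. The Sample size section sets this number on practical grounds and gives no effect size, SD or power, so there is nothing further to reproduce.

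**Inputs.** From the article: n = 40 per arm and two-sided alpha 0.05. Assumed, because the article gives no values: the share of outcome variance explained by the covariates (R² = 0.05, 0.10, 0.20) and the prevalence of a binary prognostic factor (30% or 50%).

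**Step 1: unadjusted precision of a pairwise contrast, in SD units.**

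- 95% half-width = 1.96 × sqrt(2/40) = 0.438.
- Difference detectable with 80% power = (1.960 + 0.842) × sqrt(2/40) = 0.626.

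**Step 2: gain from adjustment, before any loss for extra parameters.** The standard error is multiplied by sqrt(1 − R²), and the effective n per arm is 40/(1 − R²).

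| Assumed R² | SE multiplier | Fall in SE | Half-width | Detectable difference | Effective n per arm |
|---|---|---|---|---|---|
| 0 | 1 | 0 | 0.438 | 0.626 | 40.0 |
| 0.05 | 0.975 | 3% | 0.427 | 0.611 | 42.1 |
| 0.10 | 0.949 | 5% | 0.416 | 0.594 | 44.4 |
| 0.20 | 0.894 | 11% | 0.392 | 0.560 | 50.0 |

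For an assumed true difference of 0.5 SD, pairwise power is 60.9% unadjusted and 63.1%, 65.4% or 70.5% at the three R² values.

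**Step 3: cost of the extra parameters.** A three-group ANOVA on 120 patients leaves 120 − 3 = 117 residual degrees of freedom. With p roughly normal covariates, the variance of a contrast is inflated on average by (117 − 1)/(117 − p − 1).

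- p = 3: 116/113 = 1.027. The net SE multiplier is sqrt(1.027 × (1 − R²)) = 0.988, 0.961 or 0.906, a fall of 1.2%, 3.9% or 9.4%.
- p = 4: 116/112 = 1.036. The net SE multiplier is 0.992, 0.965 or 0.910, a fall of 0.8%, 3.5% or 9.0%.
- Break-even R²: 1 − 113/116 = 0.026 for three covariates and 1 − 112/116 = 0.034 for four.

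**Step 4: chance imbalance without stratification.** The arms are treated as independent binomial(40, prevalence) counts. A gap of 15 points is 6 patients, and a gap of 20 points is 8.

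| Prevalence | Two given arms differ by ≥ 15 points | Two given arms differ by ≥ 20 points | Largest gap among three arms ≥ 20 points |
|---|---|---|---|
| 50% | 0.22 | 0.09 | 0.21 |
| 30% | 0.18 | 0.07 | 0.16 |

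**Step 5: what such an imbalance does.** If one binary factor at 50% prevalence carried the whole R², its effect would be sqrt(R²/0.25) = 0.45, 0.63 or 0.89 SD. A 20-point gap would then move the contrast by 0.20 times that, which is 0.09, 0.13 or 0.18 SD, against the half-width of 0.438 SD.

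**Step 6: validity.** In 20,000 simulated three-arm trials with no group effect and a prognostic covariate left out of the model, unadjusted ANOVA rejected in 4.9% at a nominal 5%.

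**The case against.** The strongest reply is that nothing stated is wrong. Under randomisation the unadjusted test keeps its error rate (step 6). A shift from chance imbalance is ordinary sampling error that the interval already covers, and by step 5 it stays well under half the interval's half-width. Simple estimates are defensible in a pilot sized on practical grounds, and an adjusted analysis may sit in an analysis plan or full protocol that is not shown. All of this stands, and it limits the point to efficiency. It does not remove it, because the article does name the comparison, and the named comparison leaves baseline data unused.

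Three stronger readings are tempting but not supported:

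- A reader might infer that the protocol itself calls these factors prognostic. The Background says of the 30% to 60% prevalence figures: "This wide range can likely be attributed to the adoption of different time points", along with diagnostic criteria and unspecified patient characteristics. That concerns how common constipation is across studies. It does not name stroke severity or care setting, and it says nothing about change in CSBMs among patients who are all constipated at entry. It lends plausibility only, mainly to time since stroke.
- A reader might infer that care setting is a recorded baseline variable. It is evident from the recruitment route but is not listed as a recorded item, and the Acupuncture group section shows that it can change on discharge. Only status at randomisation could serve as a covariate.
- A reader might infer that the stated test is biased. Step 6 shows no such thing.

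It is also fair to say that a linear model displaces the Wilcoxon branch for a diary-count outcome, so a provision for non-normal residuals is needed.

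**Conclusion.** The point holds as a desirable improvement, not as an error. The article fixes an unadjusted comparison after blocked allocation with no stratification described, while baseline CSBM and NIHSS are obtained for every participant and time since stroke must be known for eligibility. These variables are available at baseline and plausibly prognostic; the documents support no more than that. The case is firmest for baseline CSBM and NIHSS.

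The size of the loss is unknown, because it depends on an R² that the article does not give. Over the assumed range of 5% to 20%, the net fall in standard error is about 1% to 9%. Below an R² of about 3% there would be no net gain.

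**What to change.** Pre-specify a linear model (ANCOVA) for CSBMs with group, baseline CSBM, NIHSS and time since stroke. Add inpatient or outpatient status only if it is recorded, and then only as it stood at randomisation. With baseline CSBM in the model, the group differences are the same whether the response is the CSBM level or its change, so the primary outcome need not be redefined. Report adjusted group differences with 95% intervals, and give the residual SD for later sample size work. If residuals are clearly non-normal, add a robust or rank-based version as a sensitivity analysis.

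The cost is analysis wording, with no new visit or measurement. NIHSS and date of onset need to be carried into the analysis data set, not used for screening alone. The model takes three to four degrees of freedom out of about 117, and the covariates must be named before unblinding.

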#### Sample size

Since there are no previous three-armed randomized controlled trials that investigate this topic, the present study will provide effect size data for sample size calculations of subsequent large-scale randomized controlled trials. For practical reasons, a sample size of 40 per group and a total number of 120 participants will be recruited during the entire study according to outpatient and inpatient censuses of the hospital.

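### The non-normal branch names the Wilcoxon test, a two-sample test, in a three-arm trial; run as unprotected pairwise tests at 0.05 it would carry a false-positive rate of about 9% to 12%

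*Protocol article*

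**What the plan says.** The Randomization and allocation concealment section fixes the design: "Participants will be randomly assigned to one of three groups (the acupuncture group, the medication group, or the control group) using a 1:1:1 ratio". The Sample size section sets the numbers: "a sample size of 40 per group and a total number of 120 participants will be recruited".

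The primary outcome is quantitative and based on counts: "The primary outcome measure will be the change in the weekly mean number of CSBMs over the 4 weeks of the intervention", and likewise over the follow-up period.

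The Statistical analysis section sets a two-branch rule for such outcomes. First, "The Kolmogorov–Smirnov test will be applied as the normality test for quantitative variables". Then, depending on that result, "The Wilcoxon test or analysis of variance (ANOVA) will be used to compare the difference between groups". The level is given once: "The statistical significance level will be set at 0.05 (two-sided) with a 95% confidence interval".

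The Background section states the comparative hypothesis: "Our hypothesis is that the effectiveness of acupuncture is no less than that of mosapride and better than routine health care". The article does not say which pairs of arms a Wilcoxon test would compare.

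**The concern.** The two branches are offered as alternatives for the same comparison, but they are not equivalent. ANOVA gives one test of three groups. The Wilcoxon test, whether rank-sum or signed-rank, compares two samples or paired measurements. A statistician who reaches the non-normal branch and follows the text has no test that compares the three arms together. The test can then be used only on pairs.

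Two things are at stake. The 0.05 level would hold for the single ANOVA test but not for several unprotected pairwise tests, so the error rate would depend on a preliminary test of the same data. The result also has consequences: the article states a hypothesis and a significance level, and its Discussion makes a later sham-controlled comparison depend on acupuncture being found effective here.

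**Working it through.** **Inputs from the article:** three arms, 40 per arm, two-sided 0.05, and two contrasts in the hypothesis (acupuncture against mosapride, acupuncture against routine care).

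**Assumptions, not in the article:** the number of pairwise tests (two or three) and the shape of the data. The calculation covers one outcome in one period, with all three arms identical.

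**Step 1. Reproduce the stated level.** A single Kruskal-Wallis test with 40 per arm was simulated 20,000 times for each of three shapes: exponential, normal, and a skewed change in counts (on-study negative binomial averaging 1.5 per week, minus a Poisson baseline averaging 1 per week). It rejected in 0.049 to 0.050 of trials. One three-group rank test therefore meets the stated 0.05.

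**Step 2. Unprotected pairwise tests, large-sample value.** Two-sided 0.05 corresponds to |z| > 1.96 for each pair.
- All three pairs: at least one rejection means that the range of three standard normal variables exceeds 1.96 × √2 = 2.77. The studentized range tail with k = 3 gives 0.122, and 0.122 / 0.05 = 2.4.
- The two acupuncture contrasts, which share one arm: 0.090, and 0.090 / 0.05 = 1.8.
- The independence formulas give 1 − 0.95³ = 0.143 and 1 − 0.95² = 0.098. Both are too high here, because the pairs share arms.

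**Step 3. Wilcoxon rank-sum tests, simulated** (20,000 runs each; standard error of the three-pair figure about 0.002):

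| Data | Three pairs | Two contrasts | Kruskal-Wallis alone | Pairs only after significant Kruskal-Wallis |
|---|---|---|---|---|
| Exponential | 0.123 | 0.092 | 0.049 | 0.049 |
| Normal | 0.119 | 0.087 | 0.049 | 0.049 |
| Count change | 0.123 | 0.092 | 0.050 | 0.050 |

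Smaller runs of 1,500 with gamma-Poisson counts (assumed 0.8 per week at baseline, 1.5 on study, shape 1, 2 or 5) scattered more widely. All three pairs gave 0.100 to 0.134, the two contrasts 0.074 to 0.097, and Kruskal-Wallis 0.035 to 0.058.

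**Step 4. How often the branch is reached.** This depends on how the Kolmogorov–Smirnov test is run, which the article does not say. On the same assumed weekly rates:
- Uncorrected, arm by arm: at least one arm flagged in 31%, 4% and 1% of trials (shape 1, 2, 5). Error over both branches was then 0.071, 0.058 and 0.059.
- With the Lilliefors correction, arm by arm: 99%, 81% and 59%.
- Pooled over all 120 participants: 7% to 90% uncorrected, 69% to 100% with the Lilliefors correction.

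**Step 5. Why the two-stage rule controls error with three arms.** If all arms are equal, a false positive requires the three-group test to reject, which has probability about 0.05. If exactly one arm differs, only one pair is truly equal, and its own test is at 0.05. If all arms differ, no pair is truly equal. A simulation with one arm shifted by 1 SD (normal data, 4,000 runs) gave 0.047 for the equal pair.

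**The case against.** The strongest reply is that the text does not commit the trial to three tests at 0.05 each. It speaks only of comparing groups, lists no pairs, and attaches the 0.05 level to the analysis in general. Placed beside ANOVA, the word Wilcoxon may be loose naming for the three-group rank test that extends it. In that case the error is about 5% and the defect is one word. The choice of pairs and the control of multiplicity are also matters that a condensed article may leave to the full protocol or SAP. Finally, this is a pilot with a sample size set for practical reasons, meant to supply effect sizes for later trials.

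Much of this stands. A reader might infer that the plan more than doubles its false-positive rate, or that about one trial in eight would report a false difference. The documents do not support either statement as fact. The 12% needs all three pairs, whereas the hypothesis names two contrasts, for which the rate is about 9%, short of double. Both figures apply only if the normality rule selects that branch. The article gives no bowel movement rates from which to judge how likely that is, and the assumed rates give anything from 1% to 100%.

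What does not fall away is the named test. A missing multiplicity plan could sit in another document, but a two-sample test named for a three-arm comparison is a statement that this article makes. The pilot status lowers the consequence, but it does not make the test fit the design.

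**Conclusion.** The point holds in a limited form. The non-normal branch names a test that does not fit three arms, and this is an error in the text, not a silence. If the test is applied literally as unprotected pairwise tests at 0.05, the chance of at least one false positive with equal arms is about 9% (two acupuncture contrasts) to 12% (all three pairs), against about 5% for one three-group rank test. These sizes rest on the non-normal branch being selected, on no error control being set elsewhere, and on a single outcome and period. The mismatch itself rests on no assumption about the data. It deserves correction even in a pilot, because the article attaches a hypothesis, a significance level and a decision on further research to the comparison.

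**What to change.** In the Statistical analysis section, replace the Wilcoxon test with the Kruskal-Wallis test as the three-group test for non-normal data. Add that pairwise comparisons (Wilcoxon rank-sum on this branch, the corresponding pairwise comparisons after ANOVA on the other) are made at 0.05 only if the three-group test is significant at 0.05. With exactly three groups this keeps the overall error at 5% without dividing alpha. Three pairwise tests at 0.05/3 would also control it, at about 0.042 in the simulations above.

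The cost is about two sentences and slightly lower pairwise power, since a pair cannot be declared different when the three-group test is not significant. The change covers tests of difference only. It does not assess whether acupuncture is at least as effective as mosapride, which has to be handled separately.

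### A normality pre-test on the trial data chooses between comparing means and comparing ranks, so the primary comparison is not fixed in advance (minor; a cheap improvement)

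*Protocol article*

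**What the plan says.** All the relevant statements are in the protocol article.

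- Statistical analysis sets the normality check: "The Kolmogorov–Smirnov test will be applied as the normality test for quantitative variables". The choice between a Wilcoxon test and ANOVA for comparing the groups is then made "according to the results of the Kolmogorov–Smirnov test".
- The same section describes the reporting without reference to the pre-test: "The results of the quantitative data analyses will be presented as means ± standard deviation". It adds: "The statistical significance level will be set at 0.05 (two-sided) with a 95% confidence interval".
- Primary outcome measure defines the outcome as the "change in the weekly mean number of CSBMs over the 4 weeks of the intervention and the 4 weeks of the follow-up". With assessments at 4 and 8 weeks, I read this as two periods, each compared with baseline.
- Statistical analysis applies the primary analysis to two populations: "The analysis of the primary outcome will be based on both a full analysis (intention-to-treat analysis) and per-protocol sets".
- Sample size gives 40 per group and 120 in total, for practical reasons, and states the purpose: "the present study will provide effect size data for sample size calculations of subsequent large-scale randomized controlled trials". The Discussion repeats that effect sizes and variability are what a later trial will take from this one.

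**The concern.** This is a stated rule, not a detail left for an analysis plan to fill in, and the rule leaves the primary comparison open. The two branches ask different questions. ANOVA compares three means. The Wilcoxon test compares ranks and, as named, takes two samples, although the trial has three arms. The pre-test therefore changes the quantity compared and possibly the contrast as well.

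For the primary outcome the rule is applied to 2 periods × 2 analysis sets = 4 comparisons, and nothing makes the four answers agree. A report could show a test of means for weeks 1-4 and a test of ranks for weeks 5-8, with means and SDs displayed for both. On the rank branch the p-value and the displayed summary then concern different quantities, and the Wilcoxon test gives no mean difference or interval to go with them. For a pilot meant to supply an effect size and its variability, a between-arm mean difference with its interval should be the fixed product in both periods.

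**Working it through.** **Nothing to reproduce.** The article states no power, effect size, SD or dropout rate, and 3 × 40 = 120 is consistent. What can be checked is how often the rule switches method, whether it distorts error rates, and what remains estimable on the rank branch.

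**1. Switching with exactly normal data.** Take a correctly sized 5% normality test and independent periods (an assumption).
- One pooled test per period: P(different methods) = 2 × 0.05 × 0.95 = 0.095.
- Ranks used if any of the three arms fails: P(fail) = 1 − 0.95³ = 0.143, and P(different methods) = 2 × 0.143 × 0.857 = 0.245. Simulation gave 0.23.

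**2. Switching with skewed counts.** Assumptions, none from the article: gamma-Poisson CSBM counts, 40 per arm, baseline 0.8 per week, on-study means 2.5, 2.2 and 1.6 per week, gamma shape 1.5 to 6, 1,500 runs per setting. The Kolmogorov–Smirnov (K-S) test was applied to each arm or to pooled residuals, with and without the Lilliefors correction for an estimated mean and SD.

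| K-S version | P(weeks 1-4 go to ranks) | P(periods get different methods) |
|---|---|---|
| Lilliefors | 0.54 to 0.95 | 0.12 to 0.47 |
| Uncorrected | 0.03 to 0.53 | 0.05 to 0.44 |

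A separate simulation of the same kind gave about 1% to 44% for different methods. The version matters because the 5% critical distance with estimated mean and SD is about 0.139 at n = 40 and 0.082 at n = 120, against 0.210 and 0.1225 for the standard test. The standard test therefore almost never rejects data that are truly normal.

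**3. Error rates of the whole rule.** Assumptions: baseline 0.8 and on-study 1.5 per week, gamma frailty, 40 per arm, 3,000 runs per setting; ANOVA or Kruskal-Wallis according to K-S (pooled Lilliefors, pooled uncorrected, or any-arm Lilliefors).
- No treatment effect: rejection 4.6% to 5.1% under the rule, 4.8% to 5.0% with ANOVA always.
- Gains of 0.7, 0.35 and 0 CSBMs per week in the three arms:

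| Frailty shape | Power under the rule | Power, ANOVA always |
|---|---|---|
| 1 (most skewed) | 0.35 | 0.40 |
| 2 | 0.46 to 0.49 | 0.51 |
| 5 | 0.60 to 0.63 | 0.63 |

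The largest loss is 0.40 − 0.35 = 0.05.

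**4. What survives on the rank branch.** Arm means and SDs are reported in any case. With 40 per arm and a common SD, the standard error of a pairwise mean difference is SD × √(2/40) = 0.22 SD, and the 95% half-width is 1.96 × 0.22 = 0.44 SD. The mean difference, its precision and a standardized effect can all be recovered from the promised summaries.

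**The case against.** The strongest defence is that the rule is mechanical, stated in advance and applied by a statistician blinded to allocation, so nobody picks the favourable p-value. That stands. The wording gives no ground for inferring analyst discretion, and the null rejection rate stays near 5%.

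The second defence is that the pilot's product is safe. This also stands. A reader might infer that the rank branch leaves the pilot without its effect estimate. The article does not support that, because it promises means and SDs without condition and mentions a 95% confidence interval without tying it to ANOVA. What is missing is narrower: a named between-arm estimate and interval that belong to the reported test.

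Third, whether K-S is corrected, and whether it is applied per arm, pooled or to residuals, may be settled in an analysis plan not shown here. That is fair, so the silence is not counted as a fault. Settling it would make the rule reproducible, but the data would still choose the method.

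Fourth, different tests for different secondary outcomes are not in themselves an error. I agree, and the point is confined to the primary outcome.

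Finally, with a true gain of 0.7 CSBMs per week, the t-test and the Wilcoxon test disagreed on significance for acupuncture against control in 8% to 15% of simulated trials. This is not a measure of harm from the rule. Two valid tests of different quantities will sometimes disagree when an effect exists. It shows only that the choice of branch can matter to the conclusion.

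**Conclusion.** The point holds as a minor one. The primary hypothesis depends on a pre-test and can differ across the two periods and the two analysis sets. On the rank branch the p-value does not correspond to the reported means and SDs. The chance that the periods get different methods was about 1% to 47% under the assumed skewed counts, and 9.5% to about 24% with exactly normal data and independent periods. The cost in power was at most about 5 points, in a pilot with no stated power target. Neither a lost effect estimate nor an inflated false-positive rate follows. All the switching and power figures rest on assumed distributions, and on reading the primary outcome as two separate periods.

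**What to change.** In Statistical analysis, delete the sentence that makes the test depend on the Kolmogorov–Smirnov result. For the primary outcome, in both periods and both analysis sets, pre-specify one three-group comparison of mean change (ANOVA or the equivalent linear model), whatever the shape of the data. Heteroscedasticity-robust standard errors are a reasonable option but not essential. Report the between-arm mean differences with 95% confidence intervals and the SD in each arm. Keep a rank test as a named sensitivity analysis, and make it Kruskal-Wallis, since there are three arms.

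This makes the chance of switching method zero and delivers directly what the later sample size calculation needs. It costs only wording and needs no new data. The downside is that a rank test could have more power for some skewed outcomes; the sensitivity analysis would still show this. In the simulated acupuncture-control comparisons the test of means had the higher power (0.50 against 0.43, 0.65 against 0.57 and 0.72 against 0.69 for frailty shapes 1, 2 and 5).
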